### Data management and analysis plan

Data entry will be performed in EpiData software version 3.1 and then it will be transferred to STATA software (Version 13.0) where all statistical analyses will be performed. The logistic regression model will be used to assess primary and secondary outcomes of the intervention. The independent t-test will be used to compare mean of different variables between the intervention and control groups. Chi-square test will be used to investigate the association between categorical variables in intervention and control groups. Within group analysis will also be done for outcomes whether it is attributed to either text message or capacity building or both.

For the repeated anthropometric measurement, biochemical test and dietary measures, we will use generalized estimating equation (GEE) and mixed model analysis to evaluate the effects of the intervention. The analysis will adjust for potential confounders for changes in weight gain and haemoglobin including baseline socio-demographic characteristics. We will also evaluate the possible interactions between the intervention indicators and participant attributes to assess the effect of intervention. Data will be analysed by ‘intention-to-treat’ principle.

Multiple imputations will be performed to account for missing data. Results will be expressed as odds ratios (ORs) with 95% confidence intervals for primary and secondary binary outcomes. Exploratory analysis will also be carried out on participant’s sub-groups to address heterogeneity. All test will be two-tailed and *p*-value will be set at < 0.05 for statistical significance.

All the FGDs will be recorded in a voice recorder. A coding framework will be prepared based on FGDs guideline. Transcription of data will be done in Nepali (National language), and then will be translated to English. Two researchers will be involved separately for coding based on pre-identified theme in the evaluation framework. Coding will be compared for consistency. The analysis will be done manually and no other software will be used for qualitative data analysis.

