## Methods

### Study setting

The study is conducted across 6 VDCs (52 wards) of Dhanusha district of Nepal. Dhanusha is one of the 75 districts of Nepal, which is situated in the southern part (also known as ‘Terai’ in local language). VDCs are the basic political unit of the district, which is further divided into nine smaller units called wards. Each ward functions as one cluster in our study. The study area is predominantly inhabited by rural communities with agriculture as a main source of occupation (particularly vegetable farming) and the study population are relatively stable.

The district borders with Siraha, Mahottari and Sindhuli districts in the east, west and north, respectively and India in the south. The main residents of the district are from the Maithili heritage and the adult literacy rate is 69%. Administratively, the district comprises one municipality and 101 VDCs with an estimated population of 754,777 in 2011 [22]. Each VDC consists of one government health facility. According to the skilled birth attendant (SBA) policy of Nepal, the health post serves as the first contact point (birthing centre) for institutional delivery [4, 23], with the deployment of at least one staff nurse. Azonal hospital (200 beds) and a private medical college act as referral hospitals for Dhanusha and adjoining districts [24, 25].

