### Sample size estimation

The estimation of sample size was done considering the study design as two-parallel arm cluster RCT [26]. We assumed that 12% of the child births have been attended by a skilled birth attendant (SBA) at baseline in both arms and this rate will increase to 32% post- intervention in the intervention arm. 20% as the minimum difference between the two groups we would like to see after intervention with 0.80 power and 0.05 level of significance, and to account for intra-cluster correlation by taking the design effect of 2.29 for delivery attended by SBA, an adjusted sample size of 147 pregnant women in each arm is required for the study [4, 24]. With allowable 20% potential attrition, the final sample size is 177 for each arm. Thus, 354 pregnant women are estimated to be included in a trial. This number would be sufficient to detect a change in the effect sizes over a follow-up period in the intervention group as compared to control group. The study area consisted of 67,625populations (male/female ratio = 100:94) and the reported birth rate are 25.5 per 1000 per year [4], which gives an estimated 1724 expected pregnant women. Since, this study will consider the pregnant women in their second trimester, around 431 (=1724 × 0. 25) pregnant woman would be available at any point of time during a year, which is sufficient number for our study.

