### Matching

Before baseline data collection, pre-trial inventory on antenatal, delivery and postnatal care, and number of pregnancies in the study area have been obtained from respective health facilities and FCHVs’ records. We have formed matched pair of clusters consulting with village secretary, chairman of the ward and FCHV of the respective ward. There are three criteria for matching: approximately equal numbers of pregnant women in the cluster; similar or predominant ethnic group distribution in each cluster; and proportionate SBA utilization rate across the cluster. The matched pair of cluster is made within each VDC. As there are nine wards in each VDC, an odd number of clusters in the VDC have been matched with odd number of cluster with other VDC. We have selected 26 matched pairs from52 clusters of the study area. Finally, 26 pairs of clusters were randomized into intervention and control arms, each arm holding 26 clusters.

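### The analysis named for SBA use at delivery and the other once-measured binary outcomes states no adjustment for ward or matched pair, although wards were randomised in pairs and the sample size assumes a design effect of 2.29

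*Protocol article*

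**What the plan says.** The protocol article is explicit that this is a cluster trial. Under Study setting: "Each ward functions as one cluster in our study". Under Matching: "Finally, 26 pairs of clusters were randomized into intervention and control arms, each arm holding 26 clusters". The Randomization section adds that allocation was made within each pair, and SBA utilisation is one of the three matching criteria.

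The Sample size estimation section starts from the assumption that "12% of the child births have been attended by a skilled birth attendant (SBA) at baseline in both arms", rising to 32% with the intervention, and inflates the sample "to account for intra-cluster correlation by taking the design effect of 2.29 for delivery attended by SBA". The result is 147 women per arm, or 177 after an allowance for attrition.

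The Data management and analysis plan section then gives the methods:

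- For outcomes generally: "The logistic regression model will be used to assess primary and secondary outcomes of the intervention".
- For categorical variables: "Chi-square test will be used to investigate the association between categorical variables in intervention and control groups".
- For means: an independent t-test between arms.
- GEE and mixed models are named only for the repeated anthropometric, biochemical and dietary measures.

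The section mentions no ward effect, cluster-robust variance, ward-level analysis or pair term. Results for binary outcomes are to be reported as odds ratios with 95% confidence intervals.

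**The concern.** SBA use happens once per woman, at delivery. It is the primary outcome on which the trial was sized, and it lies outside the sentence on GEE and mixed models. So do four ANC visits, facility delivery and PNC visits. These outcomes are left with logistic regression and, by its wording, the chi-square test. As named, neither carries anything for ward or pair.

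The sample size section more than doubles the sample because women in the same ward are expected to resemble one another. If the test ignores that resemblance, the precision claimed for the SBA odds ratio is larger than the design delivers, and the false-positive risk exceeds the stated 5%. The Discussion part of the abstract says that a proven effect will have policy implications, so the error rate of this test matters.

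**Working it through.** **Inputs from the protocol article.** SBA rates 12% and 32%, power 0.80, level 0.05, design effect (DE) 2.29, 147 women per arm before attrition and 177 after (Sample size estimation). Two-tailed tests (Data management and analysis plan). 26 wards per arm (Matching).

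**1. Reproduce the plan's sample size.** Two proportions, unpooled variance:

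n = (1.960 + 0.842)² × (0.12 × 0.88 + 0.32 × 0.68) / 0.20² = 63.4, rounded up to 64 per arm.

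64 × 2.29 = 146.6, rounded up to 147. This matches, so the design effect is a working part of the plan. The 147 women carry the information of 147 / 2.29 = 64 independent women.

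**2. Standard error.** The true standard error is √2.29 = 1.51 times the one from an analysis that treats women as independent.

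**3. True size of a nominal 5% test.**

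Size = 2 × [1 − Φ(1.96 / √DE)] = 2 × [1 − Φ(1.96 / 1.513)] = 0.195.

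Coverage of a nominal 95% interval is 1 − 0.195, about 80%. For a true 5% level the unadjusted z would have to exceed 1.96 × 1.513 = 2.97, an unadjusted p of about 0.003.

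**4. Simulation check.** Beta-binomial data with no treatment effect, 26 wards per arm, 6 or 7 women per ward, intracluster correlation (ICC) set to give DE 2.29, no matching. The unadjusted two-proportion test rejected in 19.4% to 19.8% of trials. In a similar simulation with 7 women per ward, an unpaired t-test on ward proportions rejected in 4.8% to 5.0%.

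**5. Smaller design effects.** DE 2.0 gives 16.6%, DE 1.5 gives 11.0% and DE 1.25 gives 8.0%.

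**6. Allowing for matching.** The article gives no ICC. Women per ward are 354 / 52 = 6.8 as recruited, or 294 / 52 = 5.7 if only 2 × 147 are evaluable. From DE = 1 + (m − 1) × ICC, the implied ICC is 1.29 / 5.8 = 0.22 or 1.29 / 4.65 = 0.28. If matching removes a share r of the between-ward variance, the effective design effect is (1 − ICC) + m × ICC × (1 − r). The values of r are assumptions.

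| r | Effective DE | True size |
|---|---|---|
| 0 | 2.29 | 19.5% |
| 0.25 | 1.90 to 1.91 | 15.5% to 15.6% |
| 0.50 | 1.51 to 1.53 | 11.0% to 11.4% |
| 0.75 | 1.12 to 1.16 | 6.3% to 6.8% |

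Every row exceeds 5%.

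**The case against.** The strongest reply is that the article names a model, not its variance estimator. Logistic regression with a random ward intercept or cluster-robust variance would also fit the sentence, and a condensed article may leave that to an analysis plan that is not shown. This stands in part. A reader might infer that the plan commits to a model treating women as independent; the text does not say so. But the section is not merely silent. It names chi-square and independent t-tests between arms, which in their standard form assume independence, and it assigns correlated-data methods to a different set of outcomes. Followed as written, it leads to an analysis of SBA use without ward.

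Other points that stand:

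- The chi-square and t-tests are not tied expressly to the primary outcome and could serve descriptive comparisons. The t-test does not suit a binary outcome such as SBA use.
- There are two primary outcomes. The dietary one is surveyed repeatedly and may fall under GEE or mixed models, whose clustering level is not stated. The point should not be read as covering both.
- The 19.5% figure gives no credit for matching partly on SBA utilisation, and it depends on a design effect whose derivation for these wards is not shown.
- A reader might infer that no significant SBA result could be trusted. That goes too far. At exactly 12% against 32% with 147 per arm, the unadjusted z is 0.20 / √(0.3232 / 147) = 4.27. Divided by 1.513 it is 2.82, still significant. The risk lies with weaker results.
- The sentence "Multiple imputations will be performed to account for missing data" does not mention ward, but the contents of an imputation model are ordinary detail for an analysis plan, so this is no error.

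**Conclusion.** The point holds for SBA use and the other binary outcomes measured once per woman. The plan pays for clustering in the sample size and names no provision for it, or for the pairs, in the test. If these outcomes are analysed as named, the true size of a nominal 5% test is about 19.5% under the plan's own design effect with no gain from matching. It is roughly 6% to 16% if matching removes 75% to 25% of the between-ward variance. The range rests on assumed matching gains and a back-calculated ICC; the excess over 5% does not depend on any one of these values. Describing the false-positive rate as 20% without those conditions would be more than the document supports. Because the validity of the test on the sizing outcome is affected, the text needs correcting.

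**What to change.** Amend the Data management and analysis plan section along these lines:

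- All between-arm outcome comparisons account for ward and reflect the matched pairs. For binary outcomes, use for example mixed-effects logistic regression with a random ward effect and pair accounted for, GEE clustered on ward with a small-sample correction and pair accounted for, or a paired analysis of ward-level summaries. Name one as primary.
- In the GEE and mixed models for repeated measures, include ward as well as woman.
- Do not use individual-level chi-square or independent t-tests for between-arm outcome inference.
- Report the observed ICC for SBA use, so that the 2.29 can be judged.

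The cost is wording and analysis time. The article says that the trial is completed, so if results were obtained as the section now reads they would need re-running with ward and pair identifiers, which the allocation already supplies. No new data are needed. Confidence intervals will be wider, but the sample was sized with a design effect of 2.29 to allow for this. A paired ward-level analysis would have 25 degrees of freedom from the 26 pairs.

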**Method/design:**

MATRI-SUMAN is a 12-month cluster randomized controlled trial (RCT). The trial involves pregnant women from 52 clusters of six village development committees (VDCs) covering 66,000 populations of Dhanusha district of Nepal. In the intervention clusters, Female Community Health Volunteers (FCHVs) will receive capacity development skills through reinforcement training, supervision and monitoring skills for the promotion of health seeking behaviour among pregnant women and study participants will receive periodic promotional text messaging service about MCH components through mobile phones. A sample of 354with equal numbers in each study arm is estimated using power calculation formula. The primary outcomes of this study are the rate of utilization of skilled birth attendants and consumption of a specified diversified meal. The secondary outcomes are: four antenatal (ANC) visits, weight gain of women during pregnancy, delivery of a baby at the health facility, postnatal care (PNC) visits, positive changes in child feeding practices among mothers, performance of FCHVs in MCH service utilization.

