### Study design

This is a two-parallel arms **cluster RCT** in rural community settings, provided participants are eligible for the study. Participants are recruited from 52 study areas by research assistants with the help of FCHVs. Then participants are then randomly assigned into intervention group and control arms based on clusters with approximately equal number of participations in each group.

Baseline information is collected after allocation of the clusters in two groups. At the same time, one-day extensive reinforcement training to the FCHVs in the intervention arm is conducted. Intervention group will receive text messages in their mobile phones. The principal investigator is responsible for sending text messages to the participants once they are recruited in the study and this process will continue until the fifth-month after childbirth. There will be three assessments during follow-up period and the data will be collected during these assessment periods: between 38 and 39 weeks of gestation, during delivery, and at 7 months after child birth. During the follow-up period, monitoring and supervision of FCHVs in the intervention arm will also be done to assess their performance. Additionally, assessment of child will be carried out at birth and 7 months after birth [Fig. 1].

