Both the intervention and control groups will receive regular antenatal and postnatal care provided by the government through local health facilities. These services are free of cost at the point of delivery. Both intervention and control arms participants should make at least four ANC visits (first within 4 months, second within 6 months, third within 8 months and fourth within 9 months, respectively in nearby health facility) and three home visits (First visit at day one, second at day 3 and third at day 7) in the first 7 days after childbirth by FCHVs/CHWs as part of postnatal care service.

**Usual care:** FCHVs in the control clusters will not receive training on the MCH service package and participants (pregnant women) also will not receive any text message during study period. There will be no supervision to the FCHVs from the project side, but the monthly visit by MCHWs/CHWs to them has been made from the government side as part of regular supervision to collect integrated community health service reports including MCH service reports. Any adverse event.

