## Discussions

Maternal and child health programme is one of the priority programmes of government of Nepal as this programme is included in the SDGs. Government in developing countries, including Nepal, with significant assistance from the international bilateral and non-government organisations, have been attempting to ensure the maternal and child health care services through various plans and programmes. Efficacy of safe motherhood programme is exacerbated due to several hindrances in practical aspects at grass root level. There is still a huge gap in the provision of equity-based maternal and child health services in rural Nepal. The maternal and child health interventions for people with lower socioeconomic status residing in rural areas should be identified to recommend coherent policy alternatives.

Therefore, this trial is initiated with the main objective to assess the effectiveness of capacity building and text messaging intervention on MCH service utilization and improvement in dietary intake among pregnant women in rural communities of Dhanusha district of Nepal and it is expected that this intervention will enhance the service utilization and dietary intake among intervention group as compared to control. The unique feature of this trial is that we are focusing on two components of the intervention simultaneously. First, the capacity building of FCHVs will help to support pregnant women to enforce and promote health seeking behaviour. Second, at the same time, text messaging through mobile phone will generate demand and create awareness for service utilization and optimal intake of balanced and diversified diets among pregnant women in the study area.

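### The plan promises to attribute effects to text messaging, to capacity building or to both, but every intervention ward gets both and no ward gets one alone

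*Protocol article*

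**What the plan says.** The data management and analysis plan of the protocol article contains this commitment: "Within group analysis will also be done for outcomes whether it is attributed to either text message or capacity building or both". It is not restricted to particular outcomes, so it covers the primary ones, and it is not labelled exploratory. The subgroup analysis in the same section is.

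The rest of the article describes a two-arm comparison of a package with usual care:

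- **Design.** The sample size was worked out "considering the study design as two-parallel arm cluster RCT". Under Matching, "26 pairs of clusters were randomized into intervention and control arms, each arm holding 26 clusters".
- **Intervention wards.** The abstract (Method/design) says "In the intervention clusters, Female Community Health Volunteers (FCHVs) will receive capacity development skills through reinforcement training, supervision and monitoring skills" and, in the same sentence, that "study participants will receive periodic promotional text messaging service about MCH components through mobile phones". Study design repeats that "one-day extensive reinforcement training to the FCHVs in the intervention arm is conducted" and that the same group gets the messages. The section on text messaging describes one common message package for everyone in that arm.
- **Control wards.** The usual-care paragraph says "FCHVs in the control clusters will not receive training on the MCH service package and participants (pregnant women) also will not receive any text message".
- **Intent.** The Discussions section says: "The unique feature of this trial is that we are focusing on two components of the intervention simultaneously".

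**The concern.** To attribute an outcome to one component, some units must differ in that component while the other is held fixed. Here the two are given together or not at all, so they are completely confounded with each other.

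The phrase *within group* makes this worse, because it points to an analysis inside an arm, where assignment does not vary. Any contrast found there has to come from something other than the randomisation.

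The practical stake is the choice between funding messaging, volunteer training or both. The abstract says that the trial, if effective, will inform policy in poor-resource settings. The plan applies a two-sided 0.05 threshold to all tests, so a confounded within-arm association could be reported as significant evidence for one component.

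**Working it through.** **1. What the sample size was built for.** Inputs from Sample size estimation: 12% versus 32% attended by a skilled birth attendant, power 0.80, significance level 0.05 (two-tailed according to the analysis plan), design effect 2.29.

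- Unpooled two-proportion formula: n = (1.960 + 0.842)² × (0.12 × 0.88 + 0.32 × 0.68) / 0.20² = 63.4, rounded up to 64.
- With the design effect: 64 × 2.29 = 146.6, rounded up to 147 per arm, which is the plan's figure.
- With attrition as the plan applies it: 147 × 1.2 = 176.4, rounded up to 177 per arm, 354 in all.

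The plan's numbers are reproduced, and they serve one contrast: intervention arm versus control arm. Nothing in them is set aside for a component contrast.

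**2. What the allocation identifies.** For ward j, let S_j = 1 if text messages are assigned and C_j = 1 if capacity building is assigned.

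| Wards | S | C |
|---|---|---|
| 26 intervention | 1 | 1 |
| 26 control | 0 | 0 |
| messages only | none | none |
| capacity building only | none | none |

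Take the model mean_j = α + β_S·S_j + β_C·C_j.

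- Over all 52 wards the matrix [1, S, C] has rank 2 for 3 parameters, because S_j = C_j everywhere. Only α and the sum β_S + β_C can be estimated. An interaction term would simply join that sum.
- Within the 26 intervention wards the same matrix has rank 1. Only the arm mean can be estimated, and not even the package effect.
- For contrast, a 2×2 factorial with 13 wards per cell (52 / 4) has rank 4 for 4 parameters. It would identify both main effects and the interaction.

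**3. An illustration with the plan's own effect.** The assumed difference is 32 − 12 = 20 percentage points. The splits 20 + 0, 0 + 20 and 10 + 10, or 5 + 5 with a synergy of 10, all predict 12% in control and 32% in intervention. The randomised comparison cannot tell them apart, whatever the sample size.

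**4. Can the sentence be read in a way that works?**

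- *Exposure inside the arm* (messages noted in the diary, monthly scores of the volunteers). Both arise after randomisation. Receipt depends on the woman or on a relative who passes the message on. Volunteer performance is itself a listed secondary outcome. Such a comparison is observational and lies outside the intention-to-treat principle stated in the same section.
- *Before versus after within the arm.* This mixes the effect with advancing pregnancy and secular trend. Both components run through the same follow-up, so it would not separate them in any case. Attendance at delivery also has no baseline value in the index pregnancy.
- *Content.* The training and the messages draw on overlapping source materials, so content does not show which component acted.
- *Planned interactions.* These cross the intervention with participant attributes, not one component with the other.
- *Focus groups.* They can describe attitudes and beliefs but cannot give a quantitative component effect.

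**The case against.** The best defence is that this is one ancillary sentence. The objective, the hypotheses, the sample size and the primary outcomes all treat the intervention as a package, and no primary or secondary result depends on the attribution analysis. The article also never promises a claim for a single component, and its policy statement is conditional on the trial proving effective. Actual exposure can vary within the arm even though assignment does not, and the diaries and supervision records could show it. An exposure analysis is feasible and can be reported legitimately if it is labelled observational. A fuller analysis plan, not shown here, might carry that label.

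Much of this stands. The analysis is secondary in rank, the package comparison is untouched, and the misuse in policy is a foreseeable risk, not something the article announces. Leaving out significance tests is prudent but not strictly required. The defence does not rescue attribution, however. Variation in exposure is self-selected, so it supports description and not a causal split. No further analysis detail could change that, because the allocation is fixed.

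**Conclusion.** The concern holds. By design, 0 of 52 wards are assigned a single component, so the randomised information on the separate effect of text messaging or of capacity building is zero. Only the combined effect is identified, and inside the intervention arm not even that. The sentence as written commits the trial to a causal statement it cannot make.

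This rests on one reading: that both components were assigned to all 26 intervention wards and neither to the control wards, as every relevant section of the article says. It does not depend on the effect size, the intra-cluster correlation or the attrition rate. The consequence is limited to component claims. The package-versus-control estimate, its sample size and its interpretation are unaffected.

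**What to change.** Delete the attribution sentence from the analysis plan and replace it with a statement such as: *The trial estimates the effect of the combined package compared with usual care. The separate effects of text messaging and of FCHV capacity building cannot be estimated from this design.*

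If message receipt, diary entries or FCHV contact are examined within the intervention arm, call this descriptive process evaluation, state that the exposure was not randomised, draw no attribution to a component, and preferably give no significance tests.

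The article's Trial status section says the trial is complete, so the change applies to the analysis and the report: conclusions should be confined to the package.

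The cost is wording only. No data, sample size or valid comparison is lost. The trial gives up one claim that its design could never support.
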